# A study protocol for a double-blind randomised placebo-controlled trial evaluating the efficacy of carrageenan nasal and throat spray for COVID-19 prophylaxis—ICE-COVID

**DOI:** 10.1186/s13063-022-06685-z

**Published:** 2022-09-15

**Keywords:** COVID-19

## Abstract

**Introduction:**

At present, vaccines form the only mode of prophylaxis against COVID-19. The time needed to achieve mass global vaccination and the emergence of new variants warrants continued research into other COVID-19 prevention strategies. The severity of COVID-19 infection is thought to be associated with the initial viral load, and for infection to occur, viruses including SARS-CoV-2 must first penetrate the respiratory mucus and attach to the host cell surface receptors. Carrageenan, a sulphated polysaccharide extracted from red edible seaweed, has shown efficacy against a wide range of viruses in clinical trials through the prevention of viral entry into respiratory host cells. Carrageenan has also demonstrated in vitro activity against SARS-CoV-2.

**Methods and analysis:**

A single-centre, randomised, double-blinded, placebo-controlled phase III trial was designed. Participants randomised in a 1:1 allocation to either the treatment arm, verum Coldamaris plus (1.2 mg iota-carrageenan (Carragelose®), 0.4 mg kappa-carrageenan, 0.5% sodium chloride and purified water), or placebo arm, Coldamaris sine (0.5% sodium chloride) spray applied daily to their nose and throat for 8 weeks, while completing a daily symptom tracker questionnaire for a total of 10 weeks.

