### Hypothesis

That carrageenan nasal sprays will reduce SARS-CoV-2 attachment to naso- and oropharyngeal mucosal epithelial cells and either a) prevent infection or b) reduce the severity and sequelae of resultant COVID-19 infection (through reduced effective viral infective dose exposure).

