### Treatment arms/intervention

Participants will be randomly allocated to each of either the treatment arm (verum Coldamaris plus, 1 ml of the solution containing 1.2 mg iota-carrageenan (Carragelose®), 0.4 mg kappa-carrageenan, 0.5% sodium chloride and purified water) or placebo (Coldamaris sine, saline 0.5%) arm. Coldamaris plus is a CE marked device Directive 2001/20 and GMP-Directive 2003/94/EC. Participants will be instructed to administer the spray prophylactically into each nostril and throat 1 puff three times a day (TDS) according to the manufacturer’s instructions and will be asked to continue even if symptoms develop. The trial will run for a total of 8 weeks per participant, during which time the participants will be invited to complete a daily symptom tracker.

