#### Secondary outcomes

Severity and duration of symptoms (time taken for all symptoms to resolve, length of hospital and intensive care stay, mortality rate)Acquisition of non-COVID-19 respiratory viral infections, e.g. common cold or flu symptoms in non-COVID-19 positive participantsUsability and acceptability data of nasal and throat spray as prophylaxisEffect on quality-adjusted life years and cost-effectivenessSubsequent familial/household COVID-19 infectionBaseline haematological or questionnaire findings as predictors for acquiring COVID-19 infection or determining severity and/or duration of resultant infectionassociations between symptom severity and/or duration and prognosis with COVID-19

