#### Quality of life data

Quality of life data will be collected using the EuroQol 5-dimension, 3-level (EQ-5D-3L) patient-reported outcome measures (PROM) [50]. This widely used, patient-completed PROM gathers generic data on health-related quality of life at specific time points when completed. The EQ-5D-3L is used on the advice of the NICE 2019 position statement, recommending its use over the new EQ-5D-5L [51]. Questionnaires will be completed at enrolment, week 4 and week 10 (study end).

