#### Adverse events

Adverse events are, according to the definitions, any unfavourable or unintended event affecting participants during the study. In cases of prolongation of hospitalisation, death or significant clinical sequelae, these events are defined as serious adverse events (SAEs), the occurrence of which the study sponsor (Swansea University) will be informed within 48 h of the initial observation of the event. The study treatment period is defined as the period from the first study-related nasal and throat spray administration until 14 days after the last study-related nasal and throat spray administration. Participants will be encouraged from the outset to contact the research team at the time of an event occurring by telephone or email and all details will be documented on the SAE form. The daily symptom tracker questionnaire will also provide an opportunity for symptom monitoring and the opportunity to report any symptoms that will be flagged up to the research team via a weekly report.

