### Economic evaluation

An economic evaluation will be undertaken at day 70 post randomisation. The proposed secondary endpoints and methods for economic evaluation follow the guidance set out by NICE [54]. The primary economic analysis will be a cost-utility analysis expressed in terms of quality-adjusted life years (QALYs). Cost data based on the cost of a course of active ingredient spray will be obtained from the supplying company (Marinomed Biotech AG). A comparator cost analysis will be performed for the cost associated with developing COVID-19. A number of models will be developed, expressing the predicted cost of falling ill with COVID-19 but remaining at home, the cost associated with a short hospital stay and finally that associated with an admission to critical care. Treatment costs will include the cost of each scenario including healthcare professionals, equipment and infrastructure costs. Incremental cost-effectiveness ratios, incremental net monetary benefit and incremental net health benefit statistics will be calculated. A QALY in the range of £20,000–£30,000 will be considered acceptable in line with NICE guidance [54].

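### Follow-up stops at a fixed week 10 whatever the infection date, so severity and household outcomes of late cases are cut short in both arms; this favours the spray only if protection ends with dosing

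*Protocol article*

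**What the plan says.** The Abstract (Methods and analysis) has the "spray applied daily to their nose and throat for 8 weeks, while completing a daily symptom tracker questionnaire for a total of 10 weeks". Other sections agree on a common end. Under Quality of life data: "Questionnaires will be completed at enrolment, week 4 and week 10 (study end"). Usability and compliance also gives week 10 as the study end. Under Economic evaluation: "An economic evaluation will be undertaken at day 70 post randomisation". Under Adverse events, the treatment period runs "until 14 days after the last study-related nasal and throat spray administration", which is again week 10 if the spray is used for 8 weeks.

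Treatment arms/intervention differs, for the tracker as well as the trial: "The trial will run for a total of 8 weeks per participant, during which time the participants will be invited to complete a daily symptom". That is also a fixed end, but two weeks earlier.

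The secondary outcomes include "time taken for all symptoms to resolve, length of hospital and intensive care stay, mortality rate", and later COVID-19 infection in the family or household. The second limb of the hypothesis is that the spray will "reduce the severity and sequelae of resultant COVID-19 infection"; sequelae are not in the outcome list. For continuous secondary outcomes, naming hospital stay and symptom severity and duration, the Statistical analysis section gives means, standard deviations and a t-test as the example. It describes the secondary analyses as mainly exploratory.

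**The concern.** These outcomes happen after a participant's infection, some of them weeks after. With an end date counted from enrolment, a case starting in week 2 is watched for about eight weeks and a case starting in week 10 for days. An illness still running at the end has no resolution date. A t-test on durations must then either count it as shorter than it was or drop it.

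This shortens observation in both arms. It could also do so unequally. Weeks 9 and 10 are off spray, so if protection stops with dosing, a larger share of the spray arm's cases falls in the poorly observed period. Severity is half of the research question, so even an exploratory comparison will be read as evidence on it.

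**Working it through.** **Inputs from the article.** Spray 8 weeks (56 days); end of observation week 10 (70 days); planning rates 25% and 12.5%; 152 evaluable and 190 randomised per arm. The sample size section attaches 25% to the intervention arm. I take 25% as placebo and 12.5% as spray, in line with the hypothesis of benefit.

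**Inputs assumed.** Shape of incidence over time, whether protection continues after week 8, and the lag from onset to a later event. None is in the article, so ranges are shown.

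**The plan's own figure.** With pooled variance, n per arm = [1.960·√(2·0.1875·0.8125) + 0.842·√(0.25·0.75 + 0.125·0.875)]² / 0.125² = 151.9, so 152 per arm and 304 in total; 304/0.8 = 380. It reproduces, and nothing below changes it.

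**Step 1. Simple model: constant incidence, halved by the spray to day 56, no effect afterwards.** Relative case numbers are 56 + 14 = 70 on placebo and 28 + 14 = 42 on spray.
- Under 14 days observed: 14/70 = 20% v 14/42 = 33%.
- Under 28 days observed: 28/70 = 40% v (7 + 14)/42 = 50%.
- Mean observation after onset: 0.80·42 + 0.20·7 = 35.0 days v 0.667·42 + 0.333·7 = 30.3 days.

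The late *numbers* are equal (14 v 14). Only the late *share* differs.

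**Step 2. Models tied to the planning rates.** With constant hazard λ to day 70 and an exponential lag of mean m days, the share of later events missed is λ(e^(−70λ) − e^(−70/m)) / [(1/m − λ)(1 − e^(−70λ))]. For placebo, λ = −ln(0.75)/70 = 0.00411, which gives 9% missed at m = 7 and 35% at m = 28. The other scenarios were computed numerically.

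| Scenario | Onset in last 14 days, placebo v spray | Late cases per 152 | Capture per case, spray/placebo (m = 7 to 28) |
|---|---|---|---|
| Effect lasts to day 70 | 17.8% v 18.9% | 6.8 v 3.6 | 0.994 to 0.984 |
| Effect ends day 56; risks 25% v 12.5% by day 70 | 17.8% v 41.5% | 6.8 v 7.9 | 0.89 to 0.80 |
| 25% v 12.5% by day 56, then placebo hazard in both arms | 17.2% v 32.7% | 7.9 v 9.2 | 0.93 to 0.87 |

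Where protection ends, late numbers are close. The spray arm's excess of about one case arises because more of its participants are still uninfected at week 8.

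**Step 3. Sensitivity.** With incidence doubling or halving every 21 days, the capture ratio is 0.976 to 0.998 if the effect persists and 0.81 to 0.97 if it stops. A fixed lag of 7 to 28 days in place of an exponential one gives 0.993 to 0.971 in the first row of the table and 0.87 to 0.70 in the second.

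**Step 4. Symptom duration.** Use the Step 1 model with exponential durations of the same true mean m in both arms, cut off at day 70. The mean observed duration is m[1 − (m/14)(1 − e^(−14/m))] for onsets in the last 14 days and m[1 − (m/56)(e^(−14/m) − e^(−70/m))] for earlier onsets. At m = 14 these are 5.15 and 12.74 days. Placebo: 0.80·12.74 + 0.20·5.15 = 11.2. Spray: 0.667·12.74 + 0.333·5.15 = 10.2. The ratio is 0.91. For true means of 7, 10, 14 and 21 days the ratios are 0.94, 0.92, 0.91 and 0.90, although the spray has no effect on duration in this model.

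**Step 5. Late cases to follow (under 28 days left).** At 152 per arm: 0.40·38 + 0.50·19 = 25; at 190 per arm, 31. If the spray arm's total is taken as 42/70 of placebo, to match Step 1, the figures are 0.40·38 + 0.50·22.8 = 27, and 33.

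**The case against.** A reader might infer that an effective spray must produce more late cases, so that these comparisons are bound to flatter it. The documents do not support that. With a lasting effect the spray arm has about half as many late cases (3.6 v 6.8 per 152) and a nearly equal share. The unequal effect needs protection to end with dosing. The mucosal trapping mechanism in the Introduction makes this plausible, but no section states it.

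Further points for the plan, and what stands of them:

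- On the 10-week reading, the two weeks after the last spray give every infection that starts on spray at least 14 days of observation. This stands, and it means late cases are partly observed, not unobserved. It does not cover outcomes that take longer.
- A common horizon from randomisation is a fair intention-to-treat comparison: deaths or household infections by day 70 per randomised participant are counted over equal time. This stands, and that comparison should be kept. It does not help symptom duration, which exists only in cases.
- An onset-based comparison conditions on infection, which the spray is meant to change. This stands; such a comparison remains exploratory.
- Cases found by seroconversion alone have no onset date. This stands and limits the remedy.
- If the 8-week statement is the correct one, there is no off-spray tail and the difference between arms largely disappears. Truncation in both arms remains.
- The full protocol, which the article says is on the trial registry, may define follow-up of cases. It is not shown here; the article itself gives only the fixed end.
- The economic models are built on cost scenarios, so no effect on them is claimed.

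**Conclusion.** The point holds in a limited form. Counting the end of observation from enrolment truncates late-onset cases in both arms for symptom duration, hospital and intensive care stay, mortality and household spread. The stated mean and t-test analysis does not allow for it. On constant incidence and assumed mean lags of 7 to 28 days, about 9% to 35% of later events in the placebo arm would be missed.

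A bias between the arms is conditional. If protection ends at week 8, capture per spray case is about 0.80 to 0.93 of that per placebo case, which favours the spray modestly (more if the lags are long and nearly fixed). If protection persists, the difference is negligible: under 2% with constant incidence and exponential lags. These sizes rest on assumed incidence and lag shapes. The primary outcome and the sample size are unaffected. This is a cheap improvement to exploratory outcomes, not a flaw in the main comparison.

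**What to change.** 1. Reconcile the 8-week statement under Treatment arms/intervention with the 10-week study end given elsewhere.
2. For any participant who is symptomatic or PCR-positive with less than a fixed window left at the study end (for example 28 days from onset), continue the existing emailed tracker, with household-infection and hospital items, until the window closes.
3. Report per-case severity, duration and household outcomes over that same onset-based window in both arms, with unresolved illness treated as censored rather than entered in a t-test as complete.
4. Keep the comparison per randomised participant to day 70 alongside it, and label the per-case comparison as conditional on infection and exploratory.
5. Leave seroconversion-only cases without an onset date out of the onset-based window, and say so.
6. State that sequelae beyond the window are not assessed, and limit the second limb of the hypothesis to match.

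The primary outcome, exit visit and sample size stay as they are. The cost is up to 4 more weeks of an online questionnaire for roughly 25 to 33 people at constant incidence. At 152 per arm, with protection ending at week 8, it is about 10 if incidence halves every 21 days (5.6 + 4.3) and about 45 if it doubles (24.2 + 20.6). These counts treat every case as having an onset date, so they lean high. No visit or test is added; a few final records arrive up to 4 weeks later.

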**Primary outcome:**

Acquisition of COVID-19 infection as confirmed by a positive PCR swab taken at symptom onset or seroconversion during the study. Secondary outcomes include symptom type, severity and duration, subsequent familial/household COVID-19 infection and infection with non-COVID-19 upper respiratory tract infections. A within-trial economic evaluation will be undertaken, with effects expressed as quality-adjusted life years.

**Discussion:**

This is a single-centre, phase III, double-blind, randomised placebo-controlled clinical trial to assess whether carrageenan nasal and throat spray reduces the risk of development and severity of COVID-19. If proven effective, the self-administered prophylactic spray would have wider utility for key workers and the general population.

**Trial registration:**

NCT04590365; ClinicalTrials.gov NCT04590365. Registered on 19 October 2020.

**Supplementary Information:**

The online version contains supplementary material available at 10.1186/s13063-022-06685-z.

## Strengths and limitations of this study

A randomised placebo-controlled double-blind trialSecondary outcomes designed to improve understanding of the effects of carrageenan nasal and throat sprays on COVID-19 transmission, acquisition, severity and/or duration of resultant infection and other acute respiratory infectionsRoll out of the vaccination programme has reduced the eligible participant population from which to recruit

## Introduction

In December 2019, clusters of patients presenting with severe pneumonia of unknown origin were reported in the city of Wuhan, Hubei Provence, China. The causative organism was identified as a novel coronavirus, termed SARS-CoV-2, causing the disease known as COVID-19. In March 2020, the World Health Organization (WHO) declared a global pandemic which spread across the world despite increasingly drastic non-pharmacological interventions (social distancing, mask-wearing and lockdowns). A case fatality rate of 0.1% to over 25% has been reported [1].

SARS-CoV-2 transmission is largely via respiratory droplets (>5um, travel <1m), direct contact (touching eyes/nose/mouth) and to a lesser extent aerosolisation (smaller particles <5um, travel >1m) [2, 3]. People in prolonged close contact with an infected person are most at risk. Essential workers, especially the medical workforce, have been shown to be at a seven-fold greater risk of severe disease and hospitalisation [4–6]. Healthcare workers in patient-facing roles were three times more likely to be admitted with COVID-19 than non-patient-facing healthcare workers [7]. Furthermore, the risk of developing COVID-19 was doubled among household members of patient-facing workers, compared to those in non-patient-facing roles, when adjusted for sex, age, ethnicity, socioeconomic status, and comorbidity [7]. High viral load exposure at the onset of disease may be the cause of more serious disease in patient-facing healthcare workers [4, 7–9].

At present, vaccination and social distancing form the only mode of prophylaxis against COVID-19 [10]. Many countries have started implementing a phased vaccination rollout, however, owing to issues such as vaccine availability, achievement of mass immunisation, particularly for middle- to lower-income nations, is estimated to only be achievable by 2023 at the earliest [11]. The emergence of viral mutations [12] threatens the efficacy of our current vaccine strategy [13–19], .As such, it is imperative that other methods of transmission prevention should continue to be investigated.

Carrageenan covers a range of sulphated polysaccharides and oligosaccharides extracted from red edible seaweed. It is widely used to thicken, emulsify, and preserve food and drink, as a vegetarian and vegan alternative to gelatin, as well as in the cosmetic and pharmaceutical industry. The three commercially important carrageenans are iota-, kappa- and lambda- carrageenans, which consist of disaccharide repeating units with one, two and three sulphate ester groups respectively [20]. The in vitro antiviral activity of carrageenan was first described in 1958 when carrageenan was shown to exert a marked inhibitory effect on the growth of influenza B virus and mumps virus in embryonated chicken eggs [21]. Since then, carrageenan has shown in vitro anti-viral efficacy against a wide range of viruses [22–32]. Recently, it has been demonstrated to have in vitro antiviral activity against the novel SARS-CoV-2 [33]. In vivo clinical trial data has previously demonstrated the benefit of iota-carrageenan nasal spray in reducing the duration of symptoms of the common cold, as well as the viral load in nasal lavage, compared with saline placebo sprays [34–38]. The mechanism of action is believed to be one of preventing the binding and entry of viral particles into nasal epithelial cells [22]. In order to cause infection respiratory viruses must reach their specific host cell surface receptor by moving through respiratory fluid and mucus (10 μm depth) without any means of self-propulsion [39]. Initially, this depends on Brownian motion and eventually the positively charged virus comes close enough to the cell to be attracted via large negatively charged molecules on the cell surface known as Heparan Sulphate (HS) Proteoglycans [40]. It is thought that Carrageenan mimics the HS and can, therefore, trap the virus and prevent infection of adjacent epithelial cells [35]. Carrageenan trapped viruses are thought to be transported by mucociliary clearance to the nasopharynx, swallowed, and then destroyed in stomach acid.

SARS-CoV-2 is detected in both the nose and throat, with higher viral loads in the nose [8]. Carageenan nasal and throat spray thus has potential as an ideal prevention and early treatment for COVID-19 because of several characteristics; safety, tolerability, lack of interaction with other medication and a non-specific action against different groups of viruses including emerging variants of the same virus [35]. This protocol is written in accordance with the SPIRIT checklist.

### Research question

“Does carrageenan nose and throat spray prevent or reduce the severity of COVID-19?”. This is addressed using the PICO format in Fig. 1.

**Fig. 1 Fig1:**
[figure not shown]
ICE-COVID research question (PICO format)

### Design

The design is shown in Fig. 1.

### Hypothesis

That carrageenan nasal sprays will reduce SARS-CoV-2 attachment to naso- and oropharyngeal mucosal epithelial cells and either a) prevent infection or b) reduce the severity and sequelae of resultant COVID-19 infection (through reduced effective viral infective dose exposure).

### Objectives

#### Primary objective

To determine whether carrageenan nasal and throat spray reduces the risk of COVID-19.

#### Secondary objectives

To determine:Whether carrageenan nasal and throat spray reduces the severity and/or duration of COVID-19 infection.Whether carrageenan nasal and throat spray reduces the risk of infection with other respiratory virusesThe usability of carrageenan nasal and throat spray for long-term prophylaxis against respiratory virusesThe effect of using the spray on quality-adjusted life years and cost-effectivenessWhether carrageenan nasal and throat spray reduces subsequent familial or household infection with COVID-19Whether any investigations or questionnaire findings in this trial offer a predictive value for acquiring COVID-19 infection or determining the severity and/or duration of resultant infectionAny associations between symptom severity and/or duration and prognosis with COVID-19

## Methods and analysis

### ICE-COVID trial design

Efficacy of iota-carrageenan endonasal and throat spray against COVID-19 (ICE-COVID) is a single-centre, phase III, double-blind, randomised placebo-controlled clinical trial. Participants will be randomly allocated to each of either the treatment arm (verum Coldamaris plus) or placebo (Coldamaris sine) arm (Fig. 2). Allocation to each group, treatment or placebo administration and data analysis will be blinded to both participant and investigator (double-blind).

